### Sample size

Assuming a student response rate of 40%, 1600 completed questionnaires will be available for analysis, an average of 32 students per hall. Assuming an intra-cluster correlation of 0.03, fifty halls of residence will therefore provide 80% power to detect a 0.2 standard deviation difference in units of alcohol consumed using a two-tailed alpha of 0.05.

Assuming a student response rate of 25%, 1000 completed questionnaires will be available for analysis, an average of 20 students per hall. Assuming an intra-cluster correlation of 0.03, fifty halls of residence will therefore provide 80% power to detect a 0.23 standard deviation difference in units of alcohol consumed using a two-tailed alpha of 0.05.

It is not anticipated that the effect size will be of this magnitude, with a much larger trial likely to be necessary to detect realistic effect sizes below 0.1 standard deviation. This study is therefore designed as an exploratory trial to assess the value of the intervention and plan a larger scale study if warranted.

### Process evaluation

Universities are complex systems, whose ethos, policies and practices may provide a context supportive of change, or of maintaining the status quo [10]. Within evaluations of complex interventions, process evaluation is crucial in order to understand what was implemented, how it was received and ultimately, how outcomes were produced. A process evaluation will run alongside the implementation of the programme, throughout the 2011/12 academic year. The process evaluation is concerned with 5 core research questions:

i. What role does alcohol play in students' social life during the transition to university and throughout university life?

ii. How are the toolkit and social norms activities developed and what are their underlying logic models?

iii. How are the toolkit and social norms activities implemented?

iv. How, for whom and in what circumstances, does the toolkit brings about change in university practices

v. How, for whom and in what circumstances does the social norms intervention influence alcohol related beliefs and behaviour?

The process evaluation will encompass 1) group interviews with up to twenty 2^nd ^and 3^rd ^year students in each university focusing upon experiences of alcohol throughout student life, 2) visits by a researcher to each intervention residence hall in order to monitor the distribution and placement of materials, 3) group interviews with up to 6 students in 2 case study halls in each university (one receiving and one not receiving the social norms intervention) exploring awareness and responses to the intervention 4) interviews with stakeholders in each university involved in delivering the intervention. In addition, all residence hall wardens will be asked to complete a brief questionnaire to assess changes in practice over time. Permission will also be requested from university representatives to use routine public data gathered during audits forming part of the toolkit.

Finally, within the survey described above, to assess intervention reach, students will be asked to indicate whether they had seen the intervention materials in their own hall of residence, or in another students' hall of residence. To assess recall, students who recalled seeing any of the norms materials will be asked to identify core messages from a list. Students will also be asked whether messages within the materials were credible and relevant, and whether they felt that exposure to the materials had influenced their normative perceptions or behaviour. These questions will be identical for students in control and intervention halls, allowing assessments of contamination between trial arms. The survey also includes a number of bespoke items from the intervention survey, which informed the social norm intervention, but only where these are linked to specific intervention communications (e.g. some materials focused on round buying behaviour and alternating alcoholic and soft drinks, hence items assessing the prevalence of these behaviours are retained).

Hall of residence managers will be asked for their consent for researchers to visit halls to monitor the placement of campaign materials. Prior to group interviews, an information sheet would be provided, with participants offered the opportunity to ask questions prior to obtaining informed consent. Since part of the process evaluation requires asking different questions of intervention and control premises representatives, the research team members who conduct the process evaluation will be unblinded.

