Whilst demonstrating promise, such interventions have typically been examined in isolation from the contexts in which they operate and significant questions remain to be addressed regarding how they might be applied in practice. No such studies have taken place in Wales, with the limited number of UK based studies suffering substantial weaknesses such as high levels of attrition [9]. Furthermore, universities are complex systems, whose overall ethos, policies and practices may provide a context supportive of change, or of maintaining the status quo [10]. Interventions which aim to achieve long-term change through simply targeting cognitive factors such as normative perceptions, without addressing the characteristics of the setting which support the status quo are likely to fail in the longer term [11]. Some community-based interventions to reduce alcohol consumption in adolescents have for example been shown to be more effective in rural settings than urban settings, where impacts of the intervention are perhaps drowned out by the multitude of pro-alcohol stimuli in the urban environment [12]. In Welsh universities, university managed accommodation blocks (halls of residence) primarily house students in their first year of attendance, with approximately half of students living in halls during their first year. Given that first year students are at greatest risk of excessive alcohol consumption [5], halls of residence offer potential as a means of reaching those students most at risk for alcohol related intervention.

The proposed research therefore aims to assess the value of a social marketing-led social norms-based intervention implemented in University halls of residence across four Universities in Wales. A survey of first year students was conducted in participating universities in May 2011, in order to establish levels of drinking and the prevalence of alcohol related consequences, as well as normative perceptions. Findings from the survey fed into the development of materials by an Intervention Steering Group to communicate areas of normative misperception (e.g. the extent to which students overestimated peer drinking volume), to be distributed within halls of residence. All halls of residence participating in the study will experience a university-wide alcohol harm reduction toolkit, with half randomised to additionally receive the social norms intervention.

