An exploratory cluster randomised design with nested process evaluation will be used to identify appropriate outcome measures and data collection methods, test randomisation processes, assess the extent of contamination across trial arms and establish recruitment and retention rates and intra-cluster correlations to help inform sample size for any future definitive trial. It will also identify whether the intervention effectively mobilises the underpinning theory and that this is sufficient to bring about hypothesised responses in terms of awareness, engagement and changed perception of norms. Whilst intervention acceptability and implementation processes will be assessed within the process evaluation.

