### The intervention

The intervention is a social norm marketing campaign, which aims to correct misperceptions regarding the behaviours and social expectations of peers and in so doing influence alcohol consumption. The campaign will be delivered in two phases between October 2011 and May 2012 in intervention halls of residence in four universities and will use a variety of materials encompassing posters, beer mats/coasters, leaflets, meal planners and drinking glasses. The campaign will be implemented by university accommodation staff. Social norm messages were based on the results of a survey of first year university students conducted in study universities in late April/May 2011 which identified discrepancies between norms and behaviours. Table 1 highlights the intervention materials and main social norm messages within them.

**Table 1 T1:** Social norms intervention components and examples of core messages communicated within them

Timing	Material	Core message
October 2011	Posters	'Those around you are drinking less than you think: students overestimate what others drink by 44%' 'Most of us significantly overestimate the amount that others drink'
	
	Beer mats/coasters	'Those around you are drinking less than you think: students overestimate what others drink by 44%' 'Most of us significantly overestimate the amount that others drink'
	
	Window stickers	'Few of us approve of people who drink to the point of losing it'

January 2012	Posters	'Most students drink to feel confident, but 70% have embarrassed themselves when drunk'
	
	Drinking glasses	'Time for a break? Many students limit their drinking by including soft drinks in the night'
	
	Gender specific leaflets	Males: '86% of Males have never damaged their halls of residence when drunk' Females: 'How much do you think the average female first year student drinks? Halve it. It really is less than you think.'

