### Analysis

In order to assess exposure to intervention materials and contamination between trial arms, percentages of students within the intervention and control groups reporting having seen each of the intervention materials i) in their own hall of residence and ii) in another students' hall of residence will be examined. Among those students reporting exposure to intervention materials, percentages correctly identifying the messages within them will be calculated for each trial arm. Percentages of students reporting each level of agreement with statements regarding the credibility, relevance and perceived impacts of intervention materials will also be examined for each trial arm.

Whilst the study is likely not sufficiently powered to detect impacts on behaviour, it is likely that relatively large changes in perceived norms will be necessary to produce small changes in behaviour. Hence, regression analyses, with random terms to adjust for clustering at the hall level, and fixed terms to adjust for stratification variables, will examine differences between intervention and control participants in terms of normative perceptions for alcohol consumption and alcohol related consequences. Comparisons between trial arms will be conducted on an intention-to-treat basis. Secondary analyses would compare halls on the basis of researcher observations of whether or not materials were placed.

To inform the design of a potential large scale definitive trial with sufficient power to detect changes in behaviour, intra-cluster correlations and standard deviations will be calculated for total number of units per week. Response rates will be calculated in each trial arm. The percentage of students reporting willingness to provide hair samples will also be presented, whilst among those students reporting that they would only do so if paid, percentages reporting that each level of payment would be required would be presented.

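### As described, the exposure item and its analysis record sightings in halls only, so the contamination estimate cannot detect or rule out contact away from any hall

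*Protocol article*

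**What the plan says.** Under Process evaluation, the protocol article says that the survey will ask students "whether they had seen the intervention materials in their own hall of residence, or in another students' hall of residence". It gives the purpose as contamination as well as reach: "These questions will be identical for students in control and intervention halls, allowing assessments of contamination between trial arms". The Analysis section uses the same two places. For each material, the percentages in each arm who saw it "i) in their own hall of residence and ii) in another students' hall of residence will be examined".

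The campaign itself is placed in halls. The Background describes the materials as "to be distributed within halls of residence", and The intervention says "The campaign will be delivered in two phases between October 2011 and May 2012 in intervention halls of residence". The same section says that the campaign "will use a variety of materials encompassing posters, beer mats/coasters, leaflets, meal planners and drinking glasses", and Table 1 adds window stickers.

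Contamination is a named aim: the Background says that the trial will "assess the extent of contamination across trial arms". The abstract's Objectives list it among the design parameters to be provided, and the Discussion lists it among the things a definitive trial needs to understand.

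**The concern.** The two places describe where staff put the materials. Contamination depends on where students meet them, and that need not be the same. Beer mats, leaflets and glasses can leave the building. Intervention and control halls belong to the same universities, because all are on-campus halls and allocation is stratified by institution (Inclusion/exclusion criteria; Randomisation). A control student could therefore meet a campaign item away from any hall. Such a student has no described category and would either answer no to both places or tick a hall option that does not fit.

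At stake is the only quantitative measure of campaign exposure that the article describes. If some control students meet the campaign only outside halls and answer no, that part of contamination goes uncounted. The omission bears mainly on the control arm, since intervention residents have the materials at home. A definitive trial that again randomised halls would then be planned without knowing whether this route exists.

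**Working it through.** **Textual check**

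| Point | Where | What it gives |
|---|---|---|
| Places asked about | Process evaluation | Own hall; another student's hall |
| Places analysed | Analysis | The same two, by material and arm |
| Site of delivery | Background; The intervention | Halls; no other campus site is named |
| Type of material | The intervention, text and Table 1 | Several items are portable |
| Filter for the recall question | Process evaluation | Any recalled sighting, not worded by place |

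The main routes can then be sorted as follows:

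- A control student visits an intervention hall: covered by the second place.
- A portable item is carried into the student's own hall or another hall: covered by the first or second place.
- A portable item is met away from any hall: no described category.

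The gap is the last route only.

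**Size**

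The documents give no contamination rate, so there is no figure of the plan to reproduce. Let *h* be the share of control students who saw materials in a hall and *e* the share who saw them only elsewhere. Both are assumptions. If everyone in the second group answers no to both places:

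- true exposure = *h* + *e*
- counted exposure = *h*
- share of exposed control students missed = *e* / (*h* + *e*)

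| *h* | *e* = 0 | *e* = 2% | *e* = 5% | *e* = 10% |
|---|---|---|---|---|
| 10% | 0 | 17% | 33% | 50% |
| 20% | 0 | 9% | 20% | 33% |
| 30% | 0 | 6% | 14% | 25% |

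For example, 0.05 / (0.20 + 0.05) = 20%. The Sample size section expects 1600 questionnaires at 40% response, or about 800 per arm if evenly split. Values of *e* of 2%, 5% and 10% are then 16, 40 and 80 control students. If some of these students tick a hall option instead, the undercount is smaller, but the place is misrecorded.

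**What it could mean for a later trial**

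A common dilution inflation is 1/(1 − *c*)², where *c* is the share of control students exposed. The article does not commit to this formula, and it assumes that every exposed control student receives the full intervention effect.

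- True 30%, counted 20%: 1/0.70² = 2.04 against 1/0.80² = 1.56; ratio 1.31.
- True 15%, counted 10%: 1/0.85² = 1.384 against 1/0.90² = 1.235; ratio 1.12.

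If exposure carried only a quarter of the effect (also an assumption), the first case becomes (0.95/0.925)² = 1.055, using 1 − 0.25 × 0.20 = 0.95 and 1 − 0.25 × 0.30 = 0.925. The shortfall falls from 31% to about 5%. The 31% and 12% are therefore upper illustrations for their assumed exposure rates.

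**The case against.** The strongest reply is that the two places match the campaign. Materials go into halls, no passage puts them anywhere else, and the main route this design creates, a visit to an intervention hall, has its own category. This stands. It means that contact away from halls is a possibility that the documents leave open, and nothing in them shows it to be likely.

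A reader might infer that control-arm contamination is likely to be too low overall. The documents do not support that. The omission can lower one component only, and its size may be zero. False recognition would push the control figure up. The sign of the total error is unknown.

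A reader might also count window stickers as a route from outside the building. Table 1 gives a sticker's message, "Few of us approve of people who drink to the point of losing it", but not where the stickers were placed or which way they faced. A sticker seen on another hall might in any case be reported under the second place.

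The article condenses the questionnaire, and its full response list is not shown. That stands as a caution about the survey item. It is weaker against the Analysis section, which numbers the two places to be examined and describes no line for a third.

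Other sources help only in part. Group interviews in one control hall per university, with up to 6 students, could bring contact elsewhere to light but cannot give a rate. Place of residence identifies the student's hall, and so the arm, but not the exposure. Message recall is analysed among students who report exposure. Whether someone exposed only elsewhere enters that group depends on how the filter is applied.

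**Conclusion.** The point holds in a limited form. As described, the exposure item and its analysis yield an estimate of hall-based exposure, and they cannot show whether contact away from any hall occurred. That component may be undercounted in control students. Its size is not in the documents. Under the assumed values above, the share of exposed control students missed runs from none to 50%, and the upper values depend wholly on those assumptions. The net direction of error in the control-arm figure is not established, and the 31% and 12% shortfalls should not be cited as expected consequences. Nothing in the article is contradictory or miscalculated here. This is a minor measurement gap, worth closing because contamination is a named output and the change is nearly free.

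**What to change.** Add a third response option, 'somewhere else', to the exposure item for each material, on web and paper. Add a matching line, 'iii) elsewhere', to the percentages in the Analysis section. Report it separately by arm, and include it in any-exposure among control students. The trial could then estimate this route or show that it is negligible.

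If the survey can no longer be changed, describe the reported figure as hall-based exposure only and say that contact elsewhere was not measured.

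The cost is one response option and one table row per material. The downside is a slightly longer item.

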## Discussion

The need to address high levels of alcohol misuse amongst UK student populations has led to a range of possible preventive approaches, including social marketing campaigns that address misperceptions of social norms. However, the lack of a strong evidence base for UK interventions highlights the need for an exploratory trial phase before large scale intervention implementation and the conduct of any definitive trial. Definitive trials require appropriate outcome measures, cost effective data collection, reliable randomisation processes, an understanding of potential contamination across trial arms and a measure of recruitment and retention rates and intra-cluster correlations to help inform sample size calculations. The current study provides the opportunity to generate such information within the context of an exploratory trial of a university halls based social norm marketing intervention. It also provides the opportunity to test the application of the theoretical assumptions underlying the social norm approach by measuring the hypothesised pathways that are posited as leading to behaviour change. These are an assessment of campaign awareness, reception and changes in normative perceptions. The challenges in facilitating such processes with a relatively low intensity interventions informed intervention development and the provision of the supportive environment toolkit and also led to a relatively large sample size for an exploratory trial, to asses such changes in intrapersonal processes. Finally the study provides an important opportunity to assess intervention acceptability and implementation processes to inform optimum intervention content and delivery in any future trial.

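### Message recall is asked only of students who report seeing the materials, so the by-arm percentages are not a randomised measure of message awareness and there is no unexposed baseline

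*Protocol article*

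**What the plan says.** In the Process evaluation section, all survey respondents are asked whether they saw the materials, in their own hall or another. Recall then depends on the answer: "students who recalled seeing any of the norms materials will be asked to identify core messages from a list". The Analysis section uses the same denominator: "Among those students reporting exposure to intervention materials, percentages correctly identifying the messages within them will be calculated for each trial arm". It names no test or model for recall.

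Reach is not filtered. The Analysis section reports, by arm, the percentages of students "reporting having seen each of the intervention materials i) in their own hall of residence and ii) in another students' hall of residence". The reason given for using the same items in both arms is contamination: "These questions will be identical for students in control and intervention halls, allowing assessments of contamination between trial arms".

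Two statements of aim bear on the item. The Background section says the trial will establish whether the theory behind the intervention is mobilised and is "sufficient to bring about hypothesised responses in terms of awareness, engagement and changed perception of norms". The Discussion lists the hypothesised pathways: "These are an assessment of campaign awareness, reception and changes in normative perceptions". The Analysis section also states, in the paragraph on the regressions for normative perceptions: "Comparisons between trial arms will be conducted on an intention-to-treat basis".

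**The concern.** Randomisation makes the two sets of halls comparable. It does not make comparable the students in each arm who say they saw a poster or a coaster. In intervention halls that group should include most of the students the campaign reached. In control halls it can include only students who met the materials elsewhere and students who misremember. Two percentages calculated on these groups and set side by side by arm invite a comparison that randomisation does not support.

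The routing also removes information that no later analysis can restore. Students who report no exposure never answer the item, so nothing shows how often a campaign message is picked by someone who has not seen it. A control student who heard a message in conversation, or who kept the message and forgot the poster, is not asked about messages at all. The trial is meant to inform a definitive study and names both awareness and contamination among its aims, so this is worth collecting properly.

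**Working it through.** The protocol states no exposure, recall or guessing rate, so there is no figure to reproduce. Its power statement concerns units of alcohol and does not bear on this item. The check below is an illustration, and every rate in it is an assumption.

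**Notation and assumed values**
- e, true exposure: 0.6 in intervention halls; 0.1 or 0.3 in control halls
- f, probability that an unexposed student reports exposure: 0, 0.1 or 0.2
- L, probability that an exposed student learns the message: 0 or 0.3
- g, probability of a correct pick without learning: 0.2 or 0.5
- All exposed students report exposure, and L, f and g are the same in both arms.

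**Formulas**
- Percentage correct among reporters (as planned): [e(L + (1−L)g) + (1−e)fg] / [e + (1−e)f]
- Percentage correct among all students (if all were asked): e(L + (1−L)g) + (1−e)g
- Between-arm difference among all students, by subtraction: (e_int − e_con) × L(1−g)

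**1. No learning (L = 0).** Recall among reporters equals g in both arms: 20% vs 20%, or 50% vs 50%. The difference is 0.

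**2. Learning, accurate self-report (L = 0.3, f = 0).** Recall among reporters is 0.3 + 0.7 × 0.2 = 44% in both arms, or 0.3 + 0.7 × 0.5 = 65% in both arms. The difference is again 0, although the campaign works. The difference among all students would be:

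| g | Control e = 0.1 | Control e = 0.3 |
|---|---|---|
| 0.2 | 0.5 × 0.3 × 0.8 = 12 points | 0.3 × 0.3 × 0.8 = 7.2 points |
| 0.5 | 0.5 × 0.3 × 0.5 = 7.5 points | 0.3 × 0.3 × 0.5 = 4.5 points |

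**3. Learning, some false reporting (L = 0.3, f = 0.1 or 0.2).** A gap now appears among reporters.
- Largest (g = 0.2, control e = 0.1, f = 0.2): intervention (0.264 + 0.016)/0.68 = 41.2%; control (0.044 + 0.036)/0.28 = 28.6%; gap 12.6 points.
- Smallest (g = 0.5, control e = 0.3, f = 0.1): intervention (0.39 + 0.02)/0.64 = 64.1%; control (0.195 + 0.035)/0.37 = 62.2%; gap 1.9 points.

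With L fixed at 0.3, the gap thus runs from 0 to 12.6 points depending on misreporting, control exposure and guessing. The all-student difference does not involve f.

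**4. Counting non-reporters as unaware.** This does not repair it. With no learning, the share who both report exposure and answer correctly is g times the reporting rate.
- g = 0.5, control e = 0.1, f = 0: 0.5 × 0.6 − 0.5 × 0.1 = 25 points
- g = 0.2, control e = 0.3, f = 0.2: 0.2 × 0.68 − 0.2 × 0.44 = 4.8 points

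These differences come from reach and guessing alone.

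The illustration treats reporters in the two arms as the same kind of student. If control reporters differ in habits or sociability, selection adds a further difference of unknown sign.

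**The case against.** The strongest reply is that the protocol plans no formal comparison here. It calculates percentages, states the restricted denominator openly and sets no success criterion on recall. The sentence on intention to treat follows the regressions on normative perceptions and need not cover recall. Campaign awareness in the sense of reach is asked in both arms without the filter, and recall given exposure is a coherent second step. The test of changed norms does not use the item. All of this stands, and it limits how far the problem reaches.

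Three stronger readings are tempting, and the documents do not support them.
- **Learning cannot be separated from guessing.** The list is not shown, and speaking of correct identification suggests that some options are incorrect. With decoys or a known chance rate, a correction among reporters could be possible. Cases 1 and 2 in the working differ in level (20% against 44% at g = 0.2), which such a correction would use. Only the contrast between arms fails to separate the two.
- **An easily guessed list could make the campaign look successful.** Nothing in the Analysis section judges success on this item.
- **The plan breaks its own intention-to-treat rule.** That holds only if the by-arm recall figures are read as arm comparisons under that rule, which the text does not say.

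The reply does not answer the data-collection point. Whatever analysis is chosen later, message data from students who do not report exposure will not exist.

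**Conclusion.** The point holds in a limited form. The routing and the denominator are both explicit, and the subsets are formed after randomisation by a self-report that the campaign affects. The by-arm recall percentages therefore cannot show whether the campaign raised message awareness. No unexposed baseline is collected, and message spread to control students who do not recall the materials is not measured.

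The consequence is confined to one descriptive process measure. Reach, perceived norms and the drinking outcomes are unaffected.

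The sizes in the working depend on assumed exposure, false-report, learning and guessing rates. They show how the measure behaves and do not predict results. The structural result, that equal learning among the exposed and accurate self-report give equal recall among reporters in both arms, does not depend on the particular values. A comparison of standard errors would not measure the problem: recall among reporters and recall among all students are different quantities, and the issue is selection rather than precision.

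**What to change.** Remove the routing rule and ask the message-identification item of every respondent in both arms. Place it after the drinking and norm questions, and after the exposure questions so that the list does not prompt reports of exposure. Make sure the list includes plausible messages that the campaign did not use.

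Report as the awareness result the between-arm difference in percentage correct among all respondents, by intention to treat, with the hall random effect and the stratification terms already planned for the norm regressions. Keep the percentage among self-reported exposed students, labelled as descriptive. Answers from students who report no exposure then give a baseline for correct picks, and in control halls a check on message spread that does not depend on remembering the materials.

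The cost is one extra question for students who report no exposure. On the paper form, item order cannot fully prevent looking ahead, so some influence on earlier answers remains possible there; the web form can enforce the order. If the survey can no longer be changed, the report should state that by-arm recall is descriptive and is not evidence for or against an effect on message awareness.
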